### Data collection procedures for measurement of outcomes

For all data collection procedures, written informed consent will be obtained from each participant prior to study enrollment in the trial.

#### Diagnosis of Plasmodium falciparum infections

*P. falciparum* parasite infections will be measured using RDTs, microscopy, and PCR, depending on the study outcome, as described below. The RDTs used in this trial are manufactured by (Standard Diagnostics Inc., Gyeonggi-do, Republic of Korea) under the brand name SD Bioline Malaria Antigen *P.f*, which detects the Histidine-rich protein 2 (HRP-2) antigen of *P. falciparum*. This RDT is approved by the WHO, Global Fund, and the Zambian Ministry of Health. RDTs are used across all data collection methods in this trial, including the parasite surveys, longitudinal cohort, fMDA and MDA rounds, and at health facilities in the study area. Detection of malaria parasite infections from microscopy is based on thick smears. Thick blood smears for microscopy will be used in the parasite surveys and the longitudinal cohort. PCR will be performed from capillary blood collected on dried blood spots (DBS) on filter paper, to identify low-density asexual and sexual stage parasite infections, as part of the parasite surveys and the longitudinal cohort.

#### Baseline and follow-up household parasite surveys

A cross-sectional survey of households in the high transmission season (April to May) in 2014, and again in 2015, will be conducted to obtain an unbiased sample of children under six-years-old (excluding those under one-month-old) for measuring primary outcome one (parasite prevalence). All children under six-years-old that slept in the house the night before the survey will be included in the sample. A complete enumeration and geo-referencing of all households in the study area serves as the sampling frame. To mitigate contamination between exposure groups (MDA, fMDA, and control) in the household sampling frame, sampling buffers of at least 1.5 km were derived for all HFCAs using GIS, in order to maintain an adequate distance between households in HFCAs with different exposure assignments (resulting in a gap of at least 3 km between sampled households in different HFCAs). A simple random sample of 47 households was then drawn within each of the 60 HFCAs (equal allocation sampling), to obtain the total sample size of 2,820 households in the 2014 baseline survey, after restricting the sampling frame for sampling buffers in GIS. The same sampling procedure will be used for the follow-up parasite survey in 2015.

Selected households during each survey round will be visited by trained survey data collectors that will administer a standardized survey questionnaire using mobile phones, based on the standard Malaria Indicator Survey (MIS) questionnaire [15]. Capillary blood from a finger prick from all children in selected households will be collected for detection of a malaria parasite infection by RDT, microscopy, and PCR. Children found to have a positive RDT will be treated for their infections with AL as per the Zambia National Malaria Treatment Guidelines [14].

#### Longitudinal cohort

*P. falciparum* infection incidence will be measured by following a cohort of individuals aged three-months-old and older (and not pregnant) for measuring primary outcome indicator two, the *P. falciparum* infection incidence rate (Fig. 4). Individuals within each HFCA and treatment group, within the high and low transmission strata, will be preselected from those registered in the household roster in selected households during the baseline household parasite survey between April and May 2014. Enrollment of individuals will start during round one (November 2014) of the fMDA and MDA interventions, and concurrently among individuals during round one in control areas visited for assessing RDT positivity.

**Fig. 4 Fig4:**
[figure not shown]
Flow chart for cohort enrollment and follow-up visit for both high and low transmission strata. *AL*: Artemether-lumefantrine; *DHAp*: Dihydroartemisinin plus piperaquine; *MDA*: Mass drug administration; *fMDA*: focal mass drug administration; *RDT*: Rapid diagnostic test; *DBL*: Dried blood spots

Capillary blood from a finger prick from all enrolled participants will be collected at the time of enrollment for detection of a malaria parasite infection by RDT, microscopy, and PCR. For individuals enrolled into the cohort from the round one of MDA HFCAs, all will be offered an appropriate dose of DHAp the same as those in the MDA study, irrespective of RDT result. For individuals enrolled into the cohort from the round one fMDA HFCAs, those testing positive by RDT or in households with any member testing positive by RDT will be offered an appropriate dose of DHAp the same as those in the fMDA study. Individuals enrolled into the cohort in control HFCAs testing positive by RDT will receive age and weight appropriate formulations of AL, as per standard of care guidelines [14].

Enrolled individuals within the MDA, fMDA, and control HFCAs will then be followed up on every four weeks from enrollment date for collection of blood for an RDT, microscopy, and DBS for PCR, until the study’s conclusion in November 2015. Any individual testing positive for circulating malaria antigen by RDT during any visit after enrollment will receive treatment of age- and weight-appropriate doses of AL, as per standard of care guidelines [14].

### Routine health information on confirmed and suspected malaria cases

Data on aggregate clinical and laboratory confirmed malaria cases and total outpatients seen are submitted on a weekly basis, through a standardized forma on data-enabled cell phones, using the District Health Information System 2 (DHIS2) rapid reporting system, from all 60 health facilities in the study area. Data from this source are accessible via a web server with password protection. This system was established in 2011 and 2012 and has been running in the catchment areas ever since. Time series data by facility week will be collated from this system to provide a passive incidence-based data set for evaluation of the impact of the MDA and fMDA interventions, as compared to a control of no mass treatment, on primary outcome three. Confirmed and total case counts will be standardized by the estimated mid-year populations of each HFCA.

### Rapid diagnostic test positivity during campaign rounds

As described above under the MDA and fMDA intervention descriptions, all individuals aged three-months-old and older in these HFCAs will be tested by RDT for detecting malaria parasite infections; this will then be used for ascertaining primary outcome four (RDT positivity) in each HFCA. RDT positivity in control areas during each of the two rounds of the MDA and fMDA interventions in 2014, and again in 2015, will be obtained through comparing RDT positivity among individuals tested as part of the monthly control cohort during the months when the MDA and fMDA rounds occur.

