### Standard of care and control group

Standard of care in Zambia, including the study area in Southern Province, consists of identification of malaria infections and clinical cases through passive case detection at local health facilities or community health workers. Zambian national policy stipulates that individuals seeking care for a fever be given a malaria diagnostic test by RDT or microscopy. Individuals with confirmed malaria are then treated with the first-line antimalarial in Zambia, which is AL. When no diagnostic test is available at a health facility, a clinical diagnosis is made based on signs and symptoms, and treatment follows the identical protocol as with RDT-confirmed malaria cases. Standard of care does not include any kind of active surveillance for malaria parasite infection or mass treatment of the population with antimalarials.

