### Primary outcome measures

Primary outcomes used to measures the impact of the MDA-DHAp and fMDA-DHAp interventions, as compared to a control of standard of care, are:Parasite prevalence during the high transmission season among children < six-years-old: defined as the proportion of children < six-years-old (≥three months to < six-years-old) with *P. falciparum* infection (based on both RDT and PCR) out of all children < six-years-old tested within the 2014 and 2015 cross-sectional parasite surveys.*P. falciparum* infection incidence rate among individuals ≥ three-months-old*:* defined as the number of individuals ≥ three-months-old with a new *P. falciparum* infection (based on PCR) divided by the total person-time observed among a cohort of individuals ≥ three-months-old followed up on for a 12-month-period.Total and confirmed outpatient (OPD) malaria case incidence and inpatient (IPD) malaria case incidence among all ages: defined as the number of OPD and IPD malaria confirmed and suspected cases per person per year, as ascertained from the routine rapid reporting system; facility catchment population size estimates will be used for the exposure denominator.RDT positivity: defined as the proportion of all individuals tested by RDT at each round of the fMDA and MDA interventions (and among a contemporaneous sample in the control group), with a positive RDT, among the population of individuals ≥ three-months-old.

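### At round two, primary outcome four compares a control cohort already tested and treated every four weeks with a campaign population that was not, so the effect on RDT positivity is likely to be attenuated or hidden

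*Protocol article*

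**What the plan says.** Under Primary outcome measures, outcome four is RDT positivity at each round among all those tested in the MDA and fMDA interventions ("and among a contemporaneous sample in the control group), with a positive RDT").

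The section Rapid diagnostic test positivity during campaign rounds gives the two sources:

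- MDA and fMDA arms: "all individuals aged three-months-old and older in these HFCAs will be tested by RDT for detecting malaria parasite infections". The sample size section expects about 5,000 per HFCA.
- Control arm: "RDT positivity among individuals tested as part of the monthly control cohort", in the months of the two rounds. The sample size section gives 750 people, 375 per stratum.

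The Longitudinal cohort section sets what happens to cohort members. At enrolment, during round one, "Individuals enrolled into the cohort in control HFCAs testing positive by RDT will receive age and weight appropriate formulations of AL". They are then seen every four weeks, and "Any individual testing positive for circulating malaria antigen by RDT during any visit after enrollment will receive treatment", again with AL. The section on the control group says: "Standard of care does not include any kind of active surveillance for malaria parasite infection".

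Cohort members come from households in the baseline survey, which were sampled "after restricting the sampling frame for sampling buffers in GIS". Pregnant women are not in the cohort. The campaign covers whole HFCAs.

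The statistical analysis section plans a chi-square test and random-intercept logistic models at each round, then trends across rounds with the control group used to remove seasonality.

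**The concern.** The two sides of the round-two contrast differ in more than the intervention. Round one ran in November–December 2014 and round two was scheduled for February to mid-March 2015. Counting enrolment, a control cohort member has therefore had about two to four test-and-treat visits before the round-two reading. The cohort supplies about 38 of roughly 5,000 people in each MDA or fMDA HFCA, so nearly everyone on that side had none of the four-weekly visits between rounds.

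Round one does not have this problem: control members are tested at enrolment before any treatment, and campaign participants are tested before DHAp is offered. For the same reason round one is a baseline. All the information on effect lies in round two, where the control has been altered by study procedures.

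The planned analysis does not remove the difference. Neither the chi-square test nor the logistic models address screening. In the trend analysis, the control group's change from round one to round two mixes season with test-and-treat, so the seasonality correction carries the distortion into the effect estimate. The weaknesses listed in the Discussion do not mention it.

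**Working it through.** **1. The plan's power figure.** Power = Φ(|p0 − p1|·√((c − 1)/v) − 1.645), with v = p0(1 − p0)/m0 + p1(1 − p1)/m1 + k²(p0² + p1²), c = 10 HFCAs per arm, one-sided 5%. This formula for cluster trials reproduces the plan's survey calculation: with 39 children per HFCA it gives 80.1% (30% to 18%, k = 0.31) and 80.0% (10% to 4%, k = 0.41).

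For outcome four, m0 = 375/10 = 37.5 and m1 = 5,000:

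- High (30% to 20%, k = 0.31): v = 0.00560 + 0.00003 + 0.01249 = 0.01812; power 72.0%.
- Low (10% to 5%, k = 0.41): v = 0.00240 + 0.00001 + 0.00210 = 0.00451; power 72.2%.

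The stated 80% is not reproduced, even with an undistorted control.

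**2. Control positivity at round two, flat hazard.** Inputs are the control infection rates in the cohort sample size section: 1.8 (high) and 0.6 (low) per person-year. If every treated positive is RDT-negative by the next visit, positivity equals the 28-day risk of new infection:

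- High: 1 − exp(−1.8 × 28/365) = 12.9%, against the assumed 30%.
- Low: 1 − exp(−0.6 × 28/365) = 4.5%, against the assumed 10%.

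A true 20% in the intervention arm would give an observed odds ratio of 0.250/0.148 = 1.69 (planned 0.58). A true 5% would give 0.0526/0.0471 = 1.12 (planned 0.47).

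**3. Seasonal hazard.** The Study site section puts high transmission in January–May, so the four weeks before a round-two reading carry more than the annual average. The documents give no split. Assume 60–70% of infections fall in those five months (5/12 year, 152 days), still with no RDT persistence:

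- High: 1 − exp(−1.8 × 0.60 × 28/152) = 18.0%; at 70%, 20.7%. Observed OR 1.14 to 0.96.
- Low: 1 − exp(−0.6 × 0.60 × 28/152) = 6.4%; at 70%, 7.4%. Observed OR 0.77 to 0.65.

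**4. RDT persistence.** The test detects HRP-2 antigen, and the documents do not say how long it stays positive after treatment. Let r be the share of treated positives still RDT-positive four weeks later (assumption, varied), and h the flat-hazard 28-day risk from step 2. Start at 30% or 10% and apply y → ry + (1 − ry)h over three visits:

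| r | High: control, OR | Low: control, OR |
|---|---|---|
| 0 | 12.9%, 1.69 | 4.5%, 1.12 |
| 0.25 | 16.6%, 1.25 | 6.0%, 0.83 |
| 0.50 | 23.4%, 0.82 | 8.8%, 0.55 |
| 0.75 | 35.2%, 0.46 | 13.7%, 0.33 |

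The control equals the planned intervention value at r of about 0.40 (high) and 0.11 (low). The downward bias is gone at about 0.66 and 0.58; above that the control reads too high.

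**5. Effect on power.** With 72% as the undistorted value, an observed control of 25% in the high stratum gives 34% and one of 22% gives 13%. In the low stratum, 8% gives 45% and 6% gives 15%.

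**The case against.** A reader might infer that the control value is certainly too low and that the trial would show the interventions as harmful. The documents do not support that. Reversal needs both a flat hazard and little persistence of the RDT signal. The protocol's own season moves the low stratum out of reversal across the range in step 3 and leaves the high stratum close to no difference. With a quarter to a half of treated positives still RDT-positive, the result runs from reversal to attenuation, and with more the downward bias goes. The incidence rates are also not a measure of RDT positivity: outcome two defines infection by PCR, and an RDT that misses some new infections would push the control lower. These points stand, and the size must be given as a range.

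It would also go too far to say that the trial's main inference fails. Outcomes one and three do not use the cohort. Outcome two screens all three arms alike. The stated primary aim does not mention RDT positivity, and the expected bias runs against the interventions, so it would not create false efficacy. Outcome four is nevertheless listed as primary, with its own power statement.

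The buffer mismatch has no known direction or size, and households are geo-referenced, so campaign data could be restricted to the same area. It is a secondary difference.

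Finally, a cohort comparison is not a comparison with standard of care either. That is true, and it is a cost of the fix.

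**Conclusion.** The concern holds as a lack of comparability at round two, which follows from the text whatever the size of the bias. The likely direction is a lowered control value and an attenuated or hidden effect; reversal is the extreme case. Without RDT persistence, control positivity would be about 13–21% in the high stratum and 4.5–7.4% in the low, where the plan assumes 30% and 10%; the lower ends assume a flat hazard and the upper ends 70% of infections in January–May. Substantial antigen persistence could remove the downward bias. Natural clearance is ignored throughout. The direction is therefore expected but not certain, and the documents do not fix the size. Round one and the other three primary outcomes are not affected by this asymmetry.

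**What to change.** Make the between-arm test for outcome four the round-two RDT result of cohort members in the MDA, fMDA and control HFCAs at the same four-weekly visit, with the round-one result as baseline. All three arms already have the same cohort, sampling buffers and visit schedule, so no new data are needed. Report campaign-wide positivity in the MDA and fMDA arms descriptively, or as a supportive comparison restricted to the same buffered area with the screening difference stated.

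The costs should be written into the plan:

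- **Precision.** With 37.5 per HFCA in both arms, v rises from 0.01812 to 0.02236 (23%) in the high stratum and from 0.00451 to 0.00577 (28%) in the low.
- **Power.** For the stated effects it is about 64% and 63%, against about 72% for the current contrast without bias, and lower still if screening reduces prevalence. The 80% statement needs correcting in either case.
- **Estimand.** The contrast becomes intervention plus four-weekly screening against four-weekly screening alone, and should be described so.

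A control sample not previously screened, taken at round two, would keep the comparison with standard of care. It needs new data: about 104 (high) and 59 (low) people per control HFCA for 80% power.

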#### Cost data

Cost data collection will be coupled with the study in order to provide numerator estimates for cost-effectiveness calculations. Cost data collection will be provider focused and will not require collection of data from intervention participants or research subjects. Data on the cost of inputs to the intervention will be collected using a review of program records and reports, invoices, budgets, expenditure reports, and interviews with intervention implementers. Interviews will be focused on resource use during the implementation of the study interventions. Where direct estimates of unit costs for inputs are not available through the above methods, data on costs will be supplemented with secondary source data, such as is available from the WHO-CHOICE database, the National Bank of Zambia, the World Bank, the International Monetary Fund, or other published literature. Economic costs will be estimated, meaning that costs from donated inputs will also be valued.

#### Sample size and statistical power

The maximum number of cluster units available was 60, split evenly with 10 clusters per MDA, fMDA, and control groups in the high and low transmission strata. Sample size was derived using a formula for CRCTs developed by Hayes and Moulton [16]. Sample sizes are estimated to assess statistical differences comparing the four primary outcomes for the MDA group against no intervention (control), and for the fMDA group against no intervention (control).

#### Baseline and follow-up household parasite surveys

##### High transmission strata

The coefficient of variation (CV) was estimated using data from a previous study of the 2012 MTAT-AL in the study area (CV = 0.31). Based on the number of clusters available in the high transmission strata (n = 10 in each of the three treatment groups, total of 30 clusters), a statistical power of 80 %, a probability of committing a type two error of 5 % (one-tailed test), and simple random sampling used to obtain the sample of children in each household survey, a sample size of 39 children under-years-old per HFCA per treatment group will be needed to detect 12 % absolute detectable difference in parasite prevalence between any two groups, from a baseline of 30 % (a 40 % relative difference, going from 30 to 18 % parasite prevalence). This detectable difference equates to a crude odds ratio of 0.51. With survey non-response assumed to be 20 %, a sample size of 470 children per treatment group (47 children per cluster), totaling 1,410 children under six-years-old per survey round will be sought (Additional file 1: Table S2). This sample size equates to a sample size of 1,410 households sampled per survey round.

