##### Low transmission strata

Based on the number of clusters available in the low transmission strata (n = 10 in each of the three treatment groups, total of 30 clusters), the observed CV (CV = 0.41), a statistical power of 80 %, a probability of committing a type two error of 5 % (one-tailed test), and simple random sampling used to obtain the sample of children in each household survey, a sample size of 39 children under six-years-old per HFCA per treatment group will be needed to detect 6 % absolute detectable difference in parasite prevalence between any two groups from a baseline of 10 % (a 60 % relative difference going from 10 to 4 % parasite prevalence). This detectable difference equates to a crude odds ratio of 0.38. With survey non-response assumed to 20 %, a sample size of 470 children per treatment group (47 children per cluster), totaling 1,410 children under six-years-old per survey round will be sought (Additional file 1: Table S2). This sample size equates to a sample size of 1,410 households sampled per survey round.

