##### Low transmission strata

The CV for infection incidence was based on estimates of OPD confirmed case incidence for HFCAs in 2012 (CV = 0.50). Based on the 30 HFCAs available in the low transmission strata, a statistical power of 80 %, a probability of committing a type two error of 5 % (one-tailed test), a sample size of 27 individuals aged three-months-old and older per HFCA (cluster) per treatment group will be needed to detect absolute detectable difference in parasite infection incidence between any two groups from an assumed baseline of 0.6 infections per person per year to 0.28 infections per person per year (a 53 % relative reduction). With a loss to follow-up rate assumed to be approximately 33 %, a sample size of 375 individuals per treatment group (38 per cluster) will be enrolled and followed up on monthly, totaling 1,125 individuals enrolled in the cohort study in the low transmission strata (Additional file 1: Table S3).

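### On the protocol's own assumptions, 47 children sought per HFCA yields 37.6 of the 39 required (49 are needed), and the low-stratum cohort's 27, 33% and 38 do not agree

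*Protocol article*

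**What the plan says.** All references are to the Protocol article.

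**Surveys.** Under Sample size and statistical power, Baseline and follow-up household parasite surveys:
- High transmission strata: "a sample size of 39 children under-years-old per HFCA per treatment group will be needed"; "With survey non-response assumed to be 20" per cent; the number then sought is "a sample size of 470 children per treatment group (47 children per cluster").
- Low transmission strata: "a sample size of 39 children under six-years-old per HFCA per treatment group will be needed"; "With survey non-response assumed to 20" per cent; again 470 per arm and 47 per cluster.
- Both strata turn 1,410 children into the same number of households: "This sample size equates to a sample size of 1,410 households sampled per survey round".

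The data collection section carries this through: "A simple random sample of 47 households was then drawn within each of the 60 HFCAs", 2,820 households in all. The abstract gives 5,640 children, which is two rounds of 2,820.

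**Cohort.** Under Longitudinal cohort, the high stratum requires 25 individuals per HFCA, assumes 33% loss and enrols 375 per arm (38 per HFCA). In the low stratum "a sample size of 27 individuals aged three-months-old and older per HFCA (cluster) per treatment group will be needed". Loss is put at approximately 33%, and enrolment is again 375 per arm (38 per cluster).

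**The concern.** If 39 responding children are needed and 20% do not respond, the number approached must be 39 divided by 0.8. The printed 47 is smaller than that. The requirement of 39 has no reserve, because it is the break-even value for 80% power in both strata. Any shortfall therefore takes the stated power below the 80% that the sample size section and the Discussion claim. The figure also sets the number of households drawn and the total in the abstract.

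The low-stratum cohort has a different inconsistency. Its stated requirement is higher than in the high stratum, the loss is about the same, yet enrolment is identical.

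**Working it through.** **Inputs (Sample size and statistical power).** 10 HFCAs per arm per stratum; 80% power; one-tailed 5%. The text labels this 5% a type two error, but the figures reproduce with it as the significance level. Surveys: CV 0.31, 30% to 18% (high); CV 0.41, 10% to 4% (low). Low-stratum cohort: CV 0.50, 0.6 to 0.28 infections per person-year.

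**Step 1: reproduce the 39.** The unmatched Hayes–Moulton formula with c = 10 clusters per arm, solved for the cluster size m, is

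m = [p0(1−p0) + p1(1−p1)] / [(c−1)(p0−p1)²/f − k²(p0²+p1²)], with f = (1.645 + 0.842)² = 6.18.

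- High: 0.3576 / (9 × 0.0144/6.18 − 0.0961 × 0.1224) = 38.9.
- Low: 0.1284 / (9 × 0.0036/6.18 − 0.1681 × 0.0116) = 39.0.

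Both agree with the printed 39.

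**Step 2: inflate for 20% non-response.**
- Division: 39/0.8 = 48.75, so 49.
- Multiplication: 39 × 1.2 = 46.8, which rounds to the printed 47.
- Yield of the printed figure: 47 × 0.8 = 37.6, which is 3.6% below 39.
- 47 suffices only if non-response is at most 1 − 39/47 = 17.0%.

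The high-stratum cohort is inflated by division: 25/0.67 = 37.3, so 38. Multiplication would give 25 × 1.33 = 33.

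| | Printed | From 39/0.8, rounded up |
|---|---|---|
| Per HFCA | 47 | 49 |
| Per arm per stratum | 470 | 490 |
| Per stratum per round | 1,410 | 1,470 |
| Per round, 60 HFCAs | 2,820 | 2,940 |
| Two rounds | 5,640 | 5,880 |

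**Step 3: survey power at 37.6.** Power = Φ(|p0−p1|/√V − 1.645), with V = {[p0(1−p0)+p1(1−p1)]/m + k²(p0²+p1²)}/9.

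- High: V = (0.3576/37.6 + 0.01176)/9 = 0.002364; Φ(0.12/0.0486 − 1.645) = 79.5%. At m = 39 it is 80.05%.
- Low: V = (0.1284/37.6 + 0.00195)/9 = 0.000596; Φ(0.06/0.0244 − 1.645) = 79.2%. At m = 39 it is 79.99%.

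**Step 4: low-stratum cohort.**
- 27/0.67 = 40.3, so 41 per HFCA, against 38 printed.
- 38 × 0.67 = 25.5 (or 37.5 × 0.67 = 25.1 from 375 per arm), against 27.
- 38 suffices only if loss is at most 1 − 27/38 = 28.9%.
- Power with the rate version of the formula, V = [(λ0+λ1)/y + k²(λ0²+λ1²)]/9: at y = 25.5, V = (0.88/25.5 + 0.25 × 0.4384)/9 = 0.0160 and Φ(0.32/0.1266 − 1.645) = 81%. At y = 27 it is 81.6%. The formula needs only about 22.3 person-years per HFCA for 80%.

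**The case against.** **The yield is not capped at one child per household.** The data collection section includes every child under six who slept in the house, so 39 is reached with 39/37.6 = 1.04 eligible children per responding household. The Study site section gives about 330,000 people in 56,000 households, or 5.9 each, so under-sixes would have to be about 17.6% of residents. The article does not give that share. Assuming 15% to 22%, the mean is 0.88 to 1.30 children per household, so the real yield could fall on either side of 39. This stands: 37.6 follows only from the one-for-one equation. It does not remove the inconsistency, because that equation is the one the sample size text prints.

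**The effect is small.** It is 0.6 points in the high stratum and 0.8 in the low. Rounding of the CV alone (0.305 to 0.315) moves high-stratum power at 39 children from 80.7% to 79.4%, as much as the shortfall does. In the low stratum, rounding (0.405 to 0.415) moves it only from 80.3% to 79.7%, so 79.2% lies slightly outside. The smallness stands, and it limits what can be claimed.

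**The multiplication by 1.2 is not printed.** This also stands. 47 is consistent with that slip, but the step is inferred, and the supplementary table cited for it is not part of the article. The mismatch among 39, 20% and 47 does not depend on how it arose.

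**Cohort losses still contribute time.** The outcome is infections per person-time observed, with visits every four weeks. If 33% are lost evenly over the year (an assumption), 38 enrolled give 38 × (0.67 + 0.165) = 31.7 person-years, above 27. The range is 25.5 (all lost at once) to 38 (all lost at the end). This removes any power concern. It leaves the printed numbers inconsistent, since the high-stratum 38 follows the convention that people lost contribute nothing.

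**Conclusion.** The point holds as an error in stated numbers. Given 39 required, 20% non-response and one child per household, 47 per HFCA is two short of 49, and survey power is about 79.5% and 79.2% rather than 80%. The low-stratum cohort's 38 does not follow from 27 and 33%, but power remains about 81% in the worst case for lost person-time. The power figures rest on the unmatched formula with 10 clusters per arm and a one-sided 5% level, which reproduces the protocol's 39.

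A reader might infer that the surveys are materially underpowered, that the totals of 2,820 and 5,640 must be raised, or that the low-stratum cohort is too small. The documents support none of these. The power loss is under one point, the household procedure may yield more than one child per household, and the cohort stays above 80%.

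**What to change.** 1. **Surveys.** Restate the figures in one of two ways. Either keep 47 per HFCA and give power as about 79% under one child per household, or replace the one-for-one equation with the expected number of eligible children per household and its source. About 1.04 per responding household restores 39.
2. **Low-stratum cohort.** Correct the text so that 27, 33% and 38 agree: give 41 as the inflated number, or keep 38 and state the yield and the loss convention. Note that power remains above 80%.

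Both are text changes with no cost in the field. The baseline survey is complete and can only be restated. A larger draw in 2015 is not needed to correct the statement.
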